**Inclusion criteria**
Primary open-angle glaucoma was diagnosed at least 3 months agoDiagnosed with mild or moderate open-angle glaucomaUse 1 or 2 kinds of glaucoma drugsAge ≥20 years oldAll participants will be required to sign an informed consent form and cooperate with the experimental procedures
**Exclusion criteria**
Accept any ophthalmic laser or surgery within 1 yearHigh myopia (≤6.0D)Use of any drugs that affect intraocular pressureVisual acuity with correction lower than 0.2Previous or existing uveitis or retinopathyUnable to receive acupuncture treatment continuously or allergic to acupuncture needlesPregnancy or breastfeedingRefusal to sign the informed consent form

### Ethical Considerations

Ethics approval was obtained from the institutional review board of China Medical University Hospital (CMUH111-REC3-210), and the trial was registered on ClinicalTrials.gov (NCT05753137). The informed consent discussion will take place before the trial. The informed consent form will be explained in clear and understandable language by a hospital doctor, and it will cover the intervention, risks, benefits, and patient rights in the trial. The informed consent form will be signed by the patients. If a patient wishes to withdraw from the trial, we will use the available data for the final analysis and accommodate their wishes accordingly. Confidentiality of information will be assured to the participants. All data will be anonymized or deidentified. As indicated on the recruitment poster, participants received NT $1000 (US $31) as compensation.

### Randomization and Allocation Concealment

The participants will be randomly assigned to 2 groups with a 1:1 ratio using random number generation in Microsoft Excel. A computer-based simple random sampling method without stratification with a 1:1 ratio will be used. After the random allocation is completed, the researchers will assign sequential numbers (1-50) to the participants and prepare 50 folders. The appearance of the folders will be identical for both groups, and the section containing the participant’s group and the intervention measures will be sealed. When participants complete the informed consent process, the acupuncturist will unseal the section and begin the acupuncture treatment.

### Blinding

Upon revealing the treatment allocation, the acupuncturist will proceed to administer acupuncture based on the patient’s assigned group. Throughout the entire experiment, all sterile needles will have the same appearance, thickness, and size. Only the acupuncturist will be aware of the patient’s group allocation.

Participants will be informed that there are 2 different acupuncture groups, but they will only receive 1 of them. In addition, they will undergo treatment in separate rooms to prevent any communication between them. At the end of the trial, participants will be orally questioned about whether they are aware of the treatment strategy they received, confirming the effectiveness of the blinding implementation. Throughout the entire study, there will be no communication between the acupuncturist and the participants, as well as between the acupuncturist and the assessors. This is to maintain the blinding of the participants, researchers, assessors, and statisticians to the group allocation.

### Interventions

Patients who meet the inclusion criteria at the Ophthalmology Clinic of China Medical University Hospital in Taiwan will be enrolled in a trial and randomly assigned to different groups. Both groups of patients will receive ophthalmic prescriptions and care. Acupuncture treatment will be performed using sterile acupuncture needles manufactured by “Jia Shun” (FDA 000470).

The acupuncturist will disinfect the acupoints using alcohol pads containing 70% alcohol. Then, they will apply acupuncture treatment by inserting the needles perpendicularly into the muscle layer, followed by up and down manipulation to induce the “De Qi” sensation in the treatment group. However, the control group will not experience the “De Qi” sensation; the needles will penetrate the skin, but the needling process will be halted as soon as the patients start feeling stimulation. During the 20-minute acupuncture session, the patients will maintain either a supine position or a sitting position. The acupuncturist is not allowed to communicate with the patients during the trial, except to inquire about the sensation of “De Qi.” In addition, after patients are enrolled in the trial, if no serious adverse events occur, the ophthalmologist evaluator will remain blinded and isolated until the completion of the trial at the 12th week to maintain the integrity of blinding in the trial.

### Treatment Group

In addition to routine ophthalmic prescription treatments, patients in the treatment group will receive traditional Chinese medicine–style acupuncture at the following bilateral acupoints once a week for 6 weeks: Fengchi (GB20), Cuanzhu (BL2), Sibai (ST2), Taiyang (EX-HN5), Hegu (LI4), and Taichong (LR3), for a total of 6 acupoints. The acupoint selection in this group is specific to treat symptoms of glaucoma. Figure 2 shows acupoints used in the treatment group.

**Figure 2 figure2:**
[figure not shown]
Acupoints used in the treatment group: Fengchi (GB20), Cuanzhu (BL2), Sibai (ST2), Taiyang (EX-HN5), Hegu (LI4), and Taichong (LR3).

### Control Group

In addition to routine ophthalmic prescription treatments, patients in the control group will receive minimum acupuncture stimulation at the following bilateral acupoints once a week for 6 weeks: Yinlingquan (SP9), Liangqiu (ST34), Xiajuxu (ST39), Yanglingquan (GB34), Shousanli (LI10), Sanyangluo (TE8), for a total of 6 acupoints. Figure 3 shows acupoints used in the control group. The nonophthalmological acupoints are not indicated for the treatment of ophthalmological pathologies and are not reported to improve ophthalmological function [16].

**Figure 3 figure3:**
[figure not shown]
Acupoints used in the control group: Yinlingquan (SP9), Liangqiu (ST34), Xiajuxu (ST39), Yanglingquan (GB34), Shousanli (LI10), and Sanyangluo (TE8).

### Outcome Measures

The primary outcome is the change in IOP as measured using the CT-80 Computerized Tonometer (TOPCON). Before the start of the trial, the participants’ baseline IOP will be measured. Subsequently, IOP data will be collected before each acupuncture treatment and 15 minutes after the treatment. By comparing these measurements, the effect of acupuncture treatment on IOP can be assessed.

The secondary outcomes include the long-term effects of acupuncture on the eyes. Baseline measurements and measurements after the completion of the sixth acupuncture session will be taken using OCTA (AngioVue, QuickVue version, Optovue Inc) to assess the vessel density of the radial peripapillary capillary and macula. In addition, VF, OCT, BCVA, central corneal thickness, and 2 questionnaires will be recorded at baseline and during follow-up at week 12. VF measurements will be conducted using the Humphrey Field Analyzer 3 (ZEISS) to measure the mean deviation, pattern SD, and VF index values. OCT imaging will be performed using the ZEISS HD-OCT model 5000, and measurements of the retinal nerve fiber layer, ganglion cell complex and symmetry, and the cup-to-disc ratio will be recorded. The 2 questionnaires used in the trial are the Glaucoma Symptom Scale (GSS; score range 0-100) and the Glaucoma Quality of Life-15 (GQL-15; score range 0-75) [17,18]. These questionnaires are used to quantify the extent of functional impairment or inconvenience in patients with glaucoma. In addition, to ensure the safety of participants during the trial and to address other relevant considerations related to the pathophysiology of glaucoma, BP and HR measurements will be taken at baseline, before and after acupuncture sessions, and during follow-up assessments. Table 1 depicts the trial schedule, illustrating the journey of patients from initiation to the completion of the trial.

**Table 1 table1:** Trial schedule, showing the journey of patients from initiation to the completion of the trial.

Time point		Enrollment	Treatment		Follow-up
		Visit day 1	Week 1-6	Week 6 (after acupuncture)	Week 12
**Eligibility screen**		✓			
**Informed consent**		✓			
**Allocation**		✓			

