**Methods:**

In this single-center randomized controlled trial, participants (N=50) with primary open-angle glaucoma will be randomly assigned to the treatment group, receiving ophthalmic acupuncture with “De Qi” sensation, or the control group, receiving minimum acupuncture stimulation on nonophthalmic acupoints. The intervention will consist of weekly acupuncture treatments for a total of 6 sessions. Participants will be assessed at 8 time points, which are baseline, during the intervention (6 times), and at a 3-month follow-up. The primary outcome measure is a change in the intraocular pressure before and after each acupuncture treatment. Secondary outcomes will include measurements of heart rate and blood pressure before and after acupuncture, best-corrected visual acuity, visual field, optical coherence tomography, optical coherence tomography angiography, the Glaucoma Symptom Scale, and the Glaucoma Quality of Life-15 questionnaire.

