**Data collection**					
	Intraocular pressure	✓	✓	✓	✓
	Blood pressure	✓	✓	✓	
	Heart rate	✓	✓	✓	
	OCTA^a^	✓		✓	
	OCT^b^	✓			✓
	BCVA^c^	✓			✓
	Visual field	✓			✓
	Central corneal thickness	✓			✓
	GSS^d^	✓			✓
	GQL-15^e^	✓			✓

^a^OCTA: optical coherence tomography angiography.

^b^OCT: optical coherence tomography.

^c^BCVA: best-corrected visual acuity.

^d^GSS: Glaucoma Symptom Scale.

^e^GQL-15: Glaucoma Quality of Life-15.

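### The only follow-up OCTA depends on having had all six acupuncture sessions, so as worded it compares completers, and early stoppers have no IOP level until week 12

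*Protocol article*

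**What the plan says.** The protocol article sets two kinds of trigger for its assessments.

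- **Tied to a session.** For IOP in weeks 1 to 6, Outcome Measures says "IOP data will be collected before each acupuncture treatment and 15 minutes after the treatment". The abstract defines the primary endpoint in the same terms: "The primary outcome measure is a change in the intraocular pressure before and after each acupuncture treatment". For OCTA it says "Baseline measurements and measurements after the completion of the sixth acupuncture session will be taken using OCTA". Table 1 ticks OCTA at enrollment and in the week 6 column, which it labels as falling after acupuncture, and nowhere else.
- **Tied to the calendar.** "Before the start of the trial, the participants’ baseline IOP will be measured". Table 1 also ticks IOP at week 12. The remaining eye outcomes follow the calendar too: "VF, OCT, BCVA, central corneal thickness, and 2 questionnaires will be recorded at baseline and during follow-up at week 12".

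On leaving, Ethical Considerations says only this: "If a patient wishes to withdraw from the trial, we will use the available data for the final analysis". Statistical Analysis handles missing data by pairwise deletion. Sample Size Calculation and Power assumes 25% dropout and randomizes 50, 25 per group. The article does not describe the assessment of a participant who stops acupuncture but stays in the trial.

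**The concern.** An outcome that is measured only after the full course of treatment exists only for those who took the full course. Whether a person takes all six sessions is decided after randomization and may depend on the arm: one group receives needling manipulated to produce a sensation at the ophthalmic points, the other minimal stimulation at nonophthalmic points. If more people stop in one arm, and stoppers differ from completers, the OCTA comparison loses the protection of randomization. Pairwise deletion then analyzes whoever has a value, and no later analysis can recover a scan that was never taken.

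The same scheduling leaves a gap in IOP. A participant who stops early but still comes to the clinic has no scheduled IOP reading until week 12, although a week 6 visit is already in the schedule. At stake are vessel density as a randomized comparison and a view of IOP level at the end of the treatment period for everyone randomized.

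**Working it through.** **1. Trace one participant through the schedule.** Take someone who has weekly sessions 1 to 3, then stops needling but still attends.

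- Session IOP readings planned: 6 × 2 = 12. Obtained: 3 × 2 = 6, that is 3 of 6 pre/post pairs.
- Next scheduled IOP: week 12, a gap of about 12 − 3 = 9 weeks.
- Follow-up OCTA: none. The condition is not met at week 6, and week 12 has no OCTA.
- Visual field, OCT, visual acuity, corneal thickness and both questionnaires: still due at week 12.

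**2. Counts at the plan's own dropout figure.** The planned 50 is 40 × 1.25. With 25% dropout, 25 × 0.75 = 18.75 per arm, or 37.5 in all, would have the follow-up OCTA, and 50 − 37.5 = 12.5 would not. This is not the number that a schedule change would rescue: the 25% is assumed dropout, which may include people who leave altogether. The article gives no figure for those who stop needling but would attend. (Whether the sample size itself is adequate is a separate matter.)

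**3. Session IOP is not completers-only.** Assume the 25% stop evenly over the six sessions. The number per arm giving a pair at session k is 25 − 6.25 × k/6: about 24.0, 22.9, 21.9, 20.8, 19.8 and 18.8. The share of planned pairs observed is 1 − 0.25 × 21/36 = 0.854, about 85%. Each session therefore compares its attendees, and data from before stopping are kept.

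**4. Bias in the OCTA comparison.** In arm j, let a proportion p_j stop, and let stoppers differ from completers by s_j. The mean over all randomized is the completer mean plus p_j × s_j. So

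completer difference − all-randomized difference = −(p_T s_T − p_C s_C).

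With a common gap s, this is (p_C − p_T) × s. The inputs below are assumptions; the average stopping rate is held at 25%.

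| Stopping, treatment vs control | s = 0.25 SD | s = 0.5 SD |
|---|---|---|
| 25% vs 25% | 0 | 0 |
| 32% vs 18% | 0.14 × 0.25 = 0.035 SD | 0.14 × 0.5 = 0.07 SD |
| 40% vs 10% | 0.30 × 0.25 = 0.075 SD | 0.30 × 0.5 = 0.15 SD |

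Entries are absolute sizes; the direction depends on which arm stops more and on the sign of s.

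**5. What measuring everyone does to the estimate.** Assume 25% stop and keep a fraction r of the completers' effect. The effect in all randomized is then 0.75 + 0.25r of the completer effect: 0.75 at r = 0 and 0.875 at r = 0.5.

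**The case against.** The case on the other side is strong on several points.

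- *IOP is not confined to sessions.* A reader might infer from "IOP data will be collected before each acupuncture treatment and 15 minutes after the treatment" that it is. Table 1 also ticks it at enrollment and week 12. This stands.
- *The primary endpoint needs a session.* A change across a treatment has no value when there is no treatment. A visit without needling can supply an IOP level but cannot restore the primary outcome. This stands. For the same reason no mmHg bias can be put on the primary outcome from a difference in level between stoppers and completers: a stable level difference cancels from a pre/post change.
- *Stopping needling is nowhere equated with leaving the trial.* A reader might infer that data collection ends automatically. The sentence in Ethical Considerations concerns withdrawal from the trial and keeps the data already gathered. The columns of Table 1 carry week labels, and nothing bars a stopper from attending at week 6. This stands, so the automatic version is not supported.
- *The exclusion criterion on continuous acupuncture.* A reader might suppose that it could remove randomized participants who miss sessions. It is an eligibility item, and Table 1 places the eligibility screen at visit day 1 only. It adds nothing to this point.
- *A condensed article may leave follow-up after stopping to the full protocol.* That is fair as to silence. It does not answer the OCTA trigger, which the article states: "measurements after the completion of the sixth acupuncture session will be taken using OCTA". A site that follows those words has no instruction to scan a participant who stopped at session three.

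**Conclusion.** The point holds in limited form. As worded, the follow-up OCTA is available only for participants who had all six sessions, so its comparison is one of completers. A participant who stops needling but still attends also has no IOP level between the last session and week 12. The primary within-session change and the week 12 outcomes are not affected by this scheduling. It would go too far to say that the whole trial becomes a comparison of completers: the session data of those who stop later are kept, and most outcomes other than OCTA have a calendar visit.

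The size of the bias cannot be established from the article. It is zero if stopping and the stopper-completer gap are equal in both arms. The 0.035 to 0.15 SD for OCTA rests entirely on the assumed unequal stopping rates and the assumed gap, and shows scale only. The reason to act is that the trigger is explicit, the loss cannot be repaired in analysis, and a suitable visit already exists.

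**What to change.** Change the protocol wording as follows.

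- Define the week 6 OCTA, IOP level, blood pressure and heart rate by calendar week since randomization, not by the number of sessions received.
- Take these, and the week 12 set, on every randomized participant who has not withdrawn consent to data collection, whatever number of sessions was received. When listing the week 12 set, settle blood pressure and heart rate: Outcome Measures includes them at follow-up, but Table 1 leaves them unticked at week 12.
- State that stopping acupuncture is not withdrawal from the trial.
- Record the date of and reason for stopping, so that stopping can be reported by arm.
- Keep the pre/post IOP pairs tied to sessions, as the primary outcome requires.

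The cost is an edit to the protocol and consent wording, effort to retain people who no longer receive needling, and an OCTA estimate that may be diluted by non-adherence (0.75 to 0.875 of the completer effect under the assumptions above). No new visit is needed. The article reports 10 participants enrolled, so a prompt change would cover most of the planned 50.

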**Acupuncture**					
	Treatment group		✓		
	Control group		✓		
**Data collection**					
	Intraocular pressure	✓	✓	✓	✓
	Blood pressure	✓	✓	✓	
	Heart rate	✓	✓	✓	
	OCTA^a^	✓		✓	
	OCT^b^	✓			✓
	BCVA^c^	✓			✓
	Visual field	✓			✓
	Central corneal thickness	✓			✓
	GSS^d^	✓			✓
	GQL-15^e^	✓			✓

^a^OCTA: optical coherence tomography angiography.

^b^OCT: optical coherence tomography.

^c^BCVA: best-corrected visual acuity.

^d^GSS: Glaucoma Symptom Scale.

^e^GQL-15: Glaucoma Quality of Life-15.

### Adverse Events

The study will document adverse reactions including the location of adverse reactions, the acupuncture site, the time of occurrence, the duration of symptoms, and the recovery status. In addition, appropriate medical resources and financial assistance, such as arranging emergency or outpatient care, will be provided to participants as needed.

### Statistical Analysis

The statistical analysis will be performed by a statistician from the [name]’s laboratory who is completely blind to patient allocation, using SPSS software (version 29.0; IBM Corp). The demographic data between the 2 groups, including sex, age, initial IOP, HR and BP, and BCVA will be compared using the 1-tailed Student *t* test. For the data from the 2 glaucoma questionnaires, a 1-way ANOVA will be used. In addition, a repeated measures analysis will be conducted in the trial. The data will be presented as mean (SD), and a *P* value of less than .05 will be considered statistically significant. Subgroup analysis will be conducted based on factors, such as age; gender; changes in IOP before and after treatment; VF, OCT, and OCTA data; and central corneal thickness, among others. In cases of small sample size, the Mann-Whitney *U* test and the Wilcoxon signed-rank test will be used if data do not follow normal distribution. Missing data will be analyzed using pairwise deletion.

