### Sample Size Calculation and Power

Assuming an effect size of 0.40 and a type I error (α) of .05, a sample size of 40 people (20 in each group) is required to achieve a statistical power of 95% CI. Assuming a dropout rate of 25%, a total of 50 people (25 in each group) is needed (Textbox 1).

Inclusion and exclusion criteria.

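### The Statistical Analysis section names baseline IOP only in a between-group significance test, states no baseline-adjusted IOP comparison, and fixes an unadjusted 1-way ANOVA for the two questionnaires

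*Protocol article*

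**What the plan says.** All places are in the protocol article.

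- **Collection.** Outcome Measures: "Before the start of the trial, the participants’ baseline IOP will be measured". The same section adds that "IOP data will be collected before each acupuncture treatment and 15 minutes after the treatment". Table 1 also ticks IOP at enrollment and at week 12. GSS, GQL-15, visual field, OCT and BCVA are recorded at baseline and week 12, and OCTA at baseline and after the sixth session.
- **Outcome.** The Abstract states: "The primary outcome measure is a change in the intraocular pressure before and after each acupuncture treatment". Outcome Measures lists the trial baseline beside the session readings and says "By comparing these measurements, the effect of acupuncture treatment on IOP can be assessed", without saying which reading is the reference.
- **Analysis.** Statistical Analysis, specifying a t test: "The demographic data between the 2 groups, including sex, age, initial IOP, HR and BP, and BCVA will be compared using the 1-tailed Student". The questionnaires get a 1-way ANOVA. Then: "In addition, a repeated measures analysis will be conducted in the trial", with no outcome, model or covariate named. Rank tests are the fallback for non-normal data.
- **Randomization.** "A computer-based simple random sampling method without stratification with a 1:1 ratio will be used".
- **Size.** "Assuming an effect size of 0.40 and a type I error (α) of .05", 20 per group are planned as evaluable and 25 per group are enrolled.

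**The concern.** A significance test between randomized arms asks whether a difference arose by chance, which is already known, and its result changes nothing in the outcome comparison. If the arms differ at baseline, only an analysis that conditions on the baseline value deals with it.

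A change score subtracts the baseline but does not condition on it. When baseline and follow-up are imperfectly correlated, the arm that happens to start higher tends to fall further through regression to the mean and looks like the better responder. A comparison of follow-up values alone errs the other way. Conditioning on the baseline removes both effects and reduces residual variance. In a trial of this size, whose own Conclusions section concedes that a modest sample may compromise power, that precision is worth having.

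**Working it through.** **Inputs.** From the document: 20 evaluable per arm, alpha .05, effect size 0.40, no stratification. Not given: the sidedness of alpha (two-sided assumed), whether 0.40 is a standardised mean difference d or Cohen's f (f = 0.40 means d = 0.80 with two groups; both are shown), and the baseline-to-follow-up correlation rho (assumed 0.3 to 0.9, equal variances).

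**Starting power.** Noncentral t, 20 per arm, 38 df: 23% at d = 0.40 and 69% at d = 0.80. Neither reproduces the 95% in Sample Size Calculation and Power. That is a separate matter; here these values serve only as the starting point.

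**Outcomes measured from the covariate itself.** With the variance of a single reading set to 1:

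- follow-up value alone: 1
- change score: 2(1 − rho)
- ANCOVA: 1 − rho²

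The ratio of ANCOVA to change score is (1 − rho²) / [2(1 − rho)] = (1 + rho)/2, a reduction of (1 − rho)/2. The reduction against the follow-up value alone is rho². For power, d is taken in SD units of the analysed change score, divided by √[(1 + rho)/2], with 37 df.

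| rho | Variance cut vs change score | Power, d = 0.80 (from 69%) | Power, d = 0.40 (from 23%) | Variance cut vs follow-up value |
|---|---|---|---|---|
| 0.3 | 35% | 86% | 33% | 9% |
| 0.5 | 25% | 81% | 30% | 25% |
| 0.7 | 15% | 76% | 27% | 49% |
| 0.9 | 5% | 71% | 24% | 81% |

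The last column is relevant to the questionnaires if the 1-way ANOVA is run on week 12 scores, and the second column if it is run on changes. The article does not say which.

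**Chance imbalance.** The baseline mean difference has standard error √(2/20) = 0.316 SD. A difference of at least one standard error arises in about 32% of such trials, and one above 0.5 SD in about 11%. A one-standard-error imbalance shifts an unadjusted change-score contrast by (1 − rho) × 0.316, which is 0.22, 0.16, 0.09 and 0.03 SD at rho 0.3, 0.5, 0.7 and 0.9. At rho 0.5 the change-score SD equals the single-reading SD, so 0.158 is 40% of an effect of 0.40 or 20% of one of 0.80.

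**Within-session change, as the Abstract defines the primary outcome.** Let V be the enrollment reading, A the pre-session reading and B the post-session reading. The share of Var(B − A) explained by V is (r_VB − r_VA)² / [2(1 − r_AB)]. A and B are taken on the same day, so their correlations with V should be close.

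- Equal correlations: 0%.
- Assumed 0.7 and 0.6, with r_AB = 0.8: 0.01/0.40 = 2.5%.
- The same with r_AB = 0.9: 0.01/0.20 = 5%.

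For session 1, adjusting for A itself gives (1 − r_AB)/2, which is 10% at r_AB = 0.8 and 5% at 0.9. The table therefore does not describe what the enrollment reading would do for this outcome.

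**The case against.** A reader might infer that the primary IOP analysis is unadjusted and that baseline IOP serves only the balance test. The document does not support either statement.

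- The repeated measures analysis is named without a model and could carry a baseline covariate. An article may leave covariates to a full protocol or analysis plan that is not shown here.
- The primary outcome is itself a change, so a pre-treatment value is already subtracted, and Outcome Measures lists the trial baseline among the readings to be compared.

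These objections stand. What can be said is that no adjustment is stated, not that adjustment was rejected.

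Two further inferences also fail. Chance imbalance does not bias the estimator over repeated randomizations; it affects the result of the particular trial. And the tabulated gains do not carry over to the within-session outcome with the enrollment reading as covariate. Modelling all readings after treatment starts, pre- and post-session together, would also replace that outcome with an average IOP level.

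The objections do not reach two items that are stated text. The test of initial IOP is specified and does nothing for the comparison. The 1-way ANOVA for the GSS and GQL-15 is specified, has no covariate by definition, and is applied to measures with baseline scores. No reason against adjustment is given.

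**Conclusion.** The point holds in limited form. The stated methods use baseline IOP in an uninformative test, state no baseline-adjusted IOP comparison, and fix an unadjusted one for the questionnaires.

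Where an outcome is measured from the same baseline that would be the covariate, the precision forgone against a change score is 5% to 35% of the variance for rho between 0.9 and 0.3. That is about 2 to 17 power points at d = 0.80 and 1 to 10 at d = 0.40. For the within-session IOP change, the enrollment reading would be expected to add little. The figures rest on assumed correlations, equal variances and 20 evaluable per arm. This is worth settling before data are analysed; it is an improvement to the plan, not a flaw that invalidates the trial.

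**What to change.** In Statistical Analysis:

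- **IOP change from the trial baseline, including week 12:** a mixed repeated-measures model with arm, visit, arm-by-visit and the enrollment IOP as covariate.
- **Within-session IOP change:** keep this estimand and adjust for the session 1 pre-needling IOP, the untreated reading from which the first change is measured. Pre-session readings at sessions 2 to 6 follow earlier treatment and should not be the covariate. Do not pool pre- and post-session readings into one level.
- **GSS, GQL-15, visual field, OCT, OCTA and BCVA:** ANCOVA on the follow-up value with the baseline value as covariate, replacing the 1-way ANOVA for the questionnaires.
- **Baseline IOP:** report it descriptively by arm and drop the significance test.

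If a full protocol or analysis plan already names these covariates, the article's wording need only be brought into line with it. The cost is text and one degree of freedom per model. All the readings are already scheduled, so no patients or visits are added, and the named software fits these models.
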